#### Analysis populations

The full analysis set will comprise all patients, allocated to treatment groups as originally randomised, irrespective of the treatment received and any subsequent deviations from the study protocol. The per protocol set will comprise patients with primary endpoint data available, whose treatment complies with the study protocol and for whom no other major protocol violations are identified. Protocol violations will be identified during a data review by the study management team, blind to allocation, and prior to locking the study database.

#### Analyses

Descriptive summary statistics will be provided for all variables at baseline and at each visit at which the variable is assessed. For continuous variables the following information will be provided: number of patients (N), mean, standard deviation, minimum, median, maximum and 25 % and 75 % quartiles. For categorical data frequency (absolute and relative) distributions will be provided. Differences between groups will be summarized according to data type and 95 % confidence intervals around these estimates will be constructed.

All inferential analyses will be conducted using two-tailed tests at the 5 % level of significance. The Holm correction (modified Bonferroni) will be employed on a family-wise basis to control for multiple comparisons of secondary outcomes.

Complete details of statistical analyses and methods, including data handling conventions, will be contained in a separate statistical analysis plan which will be finalized before the database is locked.

##### Primary efficacy analysis

The primary efficacy analysis will be conducted in the full analysis set. A Pearson’s Chi-squared test will be used to compare the proportions of subjects achieving clinical remission between the two treatment arms. The 95 % confidence interval for the odds of achieving clinical remission at week 48 will also be constructed. Analyses will be repeated in the per protocol set.

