### Statistical considerations

#### Sample size

Clinical remission (DAS28 remission) forms the basis of the primary outcome. The COMET study, reported remission rates in patients with very early RA (less than 4 months since diagnosis) treated with both ETN and MTX or MTX monotherapy of 70 % versus 35 % respectively. In patients with disease duration of less than 2 years but greater than 4 months, treatment with ETN and MTX was associated with 48 % remission rate. In the COMET study patients in the very early RA group were recruited within 4 months of RA diagnosis, using ACR 1987 criteria. In contrast, VEDERA will recruit patients within 12 months of symptom onset. Whilst all patients will meet RA criteria at the point of recruitment, ACR/EULAR 2010 criteria are being used, which identify patients at an earlier stage of the disease course than the 1987 criteria, and patients can potentially be recruited concurrently with diagnosis. It is likely that patients recruited to VEDERA will be at a similar stage in their disease course to the patients in the very early RA group in COMET, potentially an even earlier stage.

To account for the possibility that the interval between the treatment groups may not be as large as that seen in COMET a 30 % difference has been used as a basis for the sample size calculation. Assuming therefore that patients in treatment arm 1 are likely to achieve up to 70 % remission, and treatment arm 2 approximately 40 % remission; for 80 % power at the 5 % significance level and allowing for a 10 % dropout rate, at least 49 patients per arm will be required. Increasing this to 60 per arm would allow for a subgroup analysis of treatment arm 2 patients that proceed to require delayed ETN and MTX to be compared with treatment arm 1 and indeed those in arm 2 that stay on conventional therapy. This is an exploratory analysis; we estimate that 50 % of treatment arm 2 patients will require delayed ETN and MTX. With roughly 30 patients in each subgroup of treatment arm 2 we will obtain sufficiently accurate estimates of remission rates.

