##### Secondary efficacy analyses

Secondary efficacy analyses will be conducted in the full analysis set. Proportions of patients achieving remission or other binary responses will be compared between groups using Pearson’s Chi-squared tests. Changes in Gaussian-distributed continuous interval variables over time will be compared between groups using mixed between-within subjects ANOVA; if the data do not meet the assumptions of the test, approaches such as rank transformation will be used. Time to event analyses will be conducted using log-rank tests. Analyses will be repeated in the per protocol set.

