##### Missing data

For response variables (including the primary outcome) patients who discontinue study medication for lack of efficacy will be considered non-responders from that point forward. In all other instances, missing data will be addressed using multiple imputation. This technique assumes the data are missing at random; additional sensitivity analyses will include complete case analysis, best case/worst case single imputation, and imputation of a range of values to test the possible implications for the study conclusions if data are missing not at random.

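### The primary test and the ANOVA of continuous outcomes do not use baseline as a covariate, and the primary interval is for an odds rather than a between-arm effect

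*Protocol article*

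**What the plan says.** All from the protocol article.

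- **Primary efficacy analysis:** in the full analysis set, a Pearson "Chi-squared test will be used to compare the proportions of subjects achieving clinical remission between the two treatment arms". Next to this test the section plans an interval, at the 95 % level, in these words: "confidence interval for the odds of achieving clinical remission at week 48 will also be constructed". No covariate and no between-arm measure is named.
- **Analyses:** "Differences between groups will be summarized according to data type", with 95 % intervals. On testing, the section adds: "All inferential analyses will be conducted using two-tailed tests at the 5 % level of significance". Further statistical detail and data handling are left to a separate SAP.
- **Secondary efficacy analyses:** changes over time in Gaussian continuous variables "will be compared between groups using mixed between-within subjects ANOVA", with rank transformation as one fallback. Other planned analyses sends the RAMRIS score down the same route.
- **Secondary objectives:** the first is the change in MRI synovitis from baseline to week 48. Imaging assessments schedules MRI at baseline and weeks 12, 24, 48 and 96.
- **Missing data:** patients who stop study medication for lack of efficacy count as non-responders from then on. "In all other instances, missing data will be addressed using multiple imputation", and this covers the primary outcome.
- **Clinical efficacy and Table 3:** DAS28 is assessed at baseline in both arms.
- **Randomisation:** blocked 1:1, with no stratification factor named.

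**The concern.** Remission is a cut on the DAS28 scale, and patients may enter with any DAS28-ESR above 3.2. Where a patient starts plausibly bears on whether they are below 2.6 at week 48. That information is collected in everyone, and the primary comparison sets it aside.

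The research hypothesis is that first-line etanercept raises the proportion in remission compared with conventional therapy. An odds describes one group. Read literally, the planned interval does not estimate the contrast that the test examines, and the reader is left to guess between an odds ratio and a risk difference.

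For continuous outcomes, a between-within ANOVA treats the baseline value as one more repeated measurement. It does not condition on it. If all five MRI visits enter the model, the group-by-time test is also a joint test over every visit. It would include week 96, which falls in the observational period after the 48-week randomised trial, and it would not isolate the baseline-to-week-48 contrast in the objective.

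At stake are modest power on the primary endpoint, more appreciable precision on the continuous secondaries, and a clearly named primary effect.

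**Working it through.** **1. The plan's own sample size.** The section Sample size supplies the inputs. Its assumed remission rates: "patients in treatment arm 1 are likely to achieve up to 70 % remission, and treatment arm 2 approximately 40 % remission". The requirement it derives, which the next lines try to reproduce: "for 80 % power at the 5 % significance level and allowing for a 10 % dropout rate, at least 49 patients per arm will be required".

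n = [1.960 × √(2 × 0.55 × 0.45) + 0.842 × √(0.70 × 0.30 + 0.40 × 0.60)]² / 0.30² = (1.379 + 0.565)² / 0.09 ≈ 42 per arm. Dividing by 0.90 gives 47, within two patients of the stated 49. (With continuity correction it is 49 before dropout and 55 after.) The planned 60 per arm covers every variant.

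**2. Power of the planned test at 70 % v 40 %.** Power = Φ{[0.30 − 1.960 × √(0.495/n)] / √(0.45/n)}.

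- n = 60: (0.300 − 0.178) / 0.0866 = 1.41, so 92.1 %.
- n = 54 (60 less 10 % dropout): (0.300 − 0.188) / 0.0913 = 1.23, so 89.1 %.

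**3. Gain from adjusting the primary analysis.** The documents do not say how prognostic baseline DAS28-ESR is, so its odds ratio per SD is assumed, from 1.0 to 2.5. Simulation: 4,000 trials per setting, marginal rates held at 70 % and 40 %, Pearson's test against the likelihood-ratio test from a logistic model with one standardised covariate.

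| Assumed OR per SD | 60 per arm: Pearson / adjusted | 54 per arm: Pearson / adjusted | Fall in variance of standardised risk difference |
|---|---|---|---|
| 1.0 | 92.8 / 92.6 % | 88.4 / 89.2 % | 0 % |
| 1.5 | 92.1 / 92.7 % | 87.4 / 89.7 % | 2–3 % |
| 2.0 | 92.2 / 93.6 % | 88.7 / 92.2 % | 8–9 % |
| 2.5 | 92.2 / 95.6 % | 88.5 / 93.6 % | 12–14 % |

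The gain is about 0 to 3 points with 60 per arm and 1 to 5 with 54. With both rates at 40 %, Pearson's test rejected in 4.6–5.4 % of trials and the likelihood-ratio test in 5.0–5.9 %. The smallest gains are therefore not distinguishable from simulation error and this slight liberality: the 0.8 points at an odds ratio of 1.0 cannot be a real gain.

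**4. Continuous outcomes.** Take equal variance σ² at baseline and follow-up, with correlation ρ (assumed; not in the documents).

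- Change score, which is the group-by-time test when only two visits enter: variance 2σ²(1 − ρ).
- ANCOVA: variance σ²(1 − ρ²).
- Ratio: (1 − ρ²) / [2(1 − ρ)] = (1 + ρ)/2.

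| ρ | Variance ratio | Interval width, √ratio | Extra patients a change score needs, 1/ratio − 1 |
|---|---|---|---|
| 0.3 | 0.65 | 0.81 | 54 % |
| 0.5 | 0.75 | 0.87 | 33 % |
| 0.7 | 0.85 | 0.92 | 18 % |

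**5. Does pooling a chi-squared statistic over imputations lose power?** Simulation: 3,000 trials, 60 per arm, 10 % missing completely at random, 20 imputations.

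| Method | Power, 70 % v 40 % | Type I error, 40 % v 40 % |
|---|---|---|
| Log odds ratio, Rubin's rules | 88.3 % | 4.8 % |
| Chi-squared pooled by the D2 rule | 88.5 % | 5.1 % |
| Complete-case chi-squared | 88.7 % | 5.0 % |

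There is no material difference.

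**The case against.** The strongest defence is that the primary test is sound. Randomisation names no stratification factor, so no design variable is left out. Pearson's test answers a hypothesis about proportions, matches the sample-size basis and holds its level. The gain from adjustment rests on a prognostic strength that the documents do not give. The Analyses section also promises between-group differences with 95 % intervals, so a contrast will be reported, and the odds is probably loose wording for an odds ratio. All of this stands. It limits the size of the point, but it does not name the primary effect measure or put the baseline value to use.

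A reader might infer four stronger things that the documents do not support:

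- **That the primary analysis is invalid or underpowered.** At the planned rates it is neither. Power would be low if arm 2 reached 50 %: with 54 per arm, [0.20 − 1.960 × √(0.48/54)] / √(0.46/54) = 0.16, or about 57 %. That rate is not the protocol's assumption.
- **That multiple imputation makes the chi-squared test lose power.** The check shows no such loss, and the pooling rule may properly be left to the SAP. Rubin's rules matter here only because they give an estimate, interval and p-value from one source.
- **That the ANOVA ignores baseline.** It compares changes over time, so baseline enters as a time level. The fair criticism is that it is not a covariate.
- **That the ANOVA must be omnibus and depend on sphericity.** The article does not fix which visits enter. With baseline and week 48 only, the group-by-time test is exactly the change contrast and sphericity does not arise. The complaint holds only if more visits are included.

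**Conclusion.** The point holds as a matter of efficiency and of a misnamed effect, not of validity. The planned primary test has about 89 to 92 % power against a target of 80 %. Adjusting for baseline DAS28-ESR would add roughly 0 to 3 points with 60 per arm, or 1 to 5 with 54, if the odds ratio per SD lies between 1.0 and 2.5.

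The larger gain is for continuous outcomes. With baseline as a covariate, variance falls to 65–85 % of the change-score variance for correlations of 0.3 to 0.7, assuming equal variances at the two visits.

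Separately, the interval for the odds should be replaced by one for a named between-arm measure, whatever is decided on adjustment. The SAP is not among the documents reviewed. If it already makes these choices, what remains is to bring the two texts into line.

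**What to change.** **Primary.** Estimate the effect by logistic regression of week-48 remission on arm and baseline DAS28-ESR. Report the between-arm odds ratio and the standardised risk difference, each with a 95 % interval, combined over imputations by Rubin's rules. State which of them carries the primary p-value. Keep the unadjusted Pearson test as a supportive analysis.

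**Continuous secondaries.** Use ANCOVA, or a mixed model for repeated measures with visit, arm-by-visit and unstructured covariance, with the baseline value as a covariate. Test at the visit that the objective names, which is week 48 for MRI synovitis.

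**Cost.** Wording in the SAP before database lock, a little more analysis work, and no new data. The trial is open-label, so the change should be dated and made before outcomes are compared by arm. The adjusted odds ratio is conditional on baseline and will not equal the one from the raw two-by-two table, which is why the standardised risk difference is reported beside it.

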### Randomisation

Once eligibility is confirmed and all relevant procedures have been completed, participants will be block randomised 1:1 to one of the following two treatment groups (Fig. 1):Treatment Arm 1 or ‘very early ETN’ will receive ETN and MTX combination therapy administered for a total duration of 48 weeks.Treatment Arm 2 or ‘delayed ETN’ will receive initial MTX monotherapy with adoption of a TT protocol (standard care involving monthly DAS28-ESR assessment with escalation to combination sDMARD therapy if not achieving LDA at, or after, 8 weeks) and step-up to ETN and MTX at 24 weeks if failing to achieve clinical remission.

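### The primary week-48 remission test leaves out baseline DAS28-ESR: pre-specifying adjustment would be a cheap efficiency improvement, not the repair of an error

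*Protocol article*

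**What the plan says.** Protocol article, *Primary efficacy analysis*: "The primary efficacy analysis will be conducted in the full analysis set". The method is a Pearson "Chi-squared test will be used to compare the proportions of subjects achieving clinical remission between the two treatment arms". The next sentence adds: "The 95 % confidence interval for the odds of achieving clinical remission at week 48 will also be constructed". No covariate is named, and the analysis is repeated per protocol.

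*Analyses*: "All inferential analyses will be conducted using two-tailed tests at the 5 % level of significance". This section also promises between-group differences with 95 % intervals for all data types, and leaves full methods and data handling to a separate SAP.

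*Patient eligibility* (Table 1) requires DAS28-ESR above 3.2 and a known ACPA/RF status. Table 3 schedules DAS28 at screening and at baseline. *Methods of assessment* defines DAS28 remission as a value below 2.6, so the primary outcome is a later value of the same score, dichotomised.

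*Randomisation*: "participants will be block randomised 1:1 to one of the following two treatment groups". No stratification factor is mentioned.

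*Missing data*: patients who stop study medication for lack of efficacy count as non-responders. "In all other instances, missing data will be addressed using multiple imputation".

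*Other planned analyses* uses logistic regression only to explore predictors of remission.

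**The concern.** When an outcome is a dichotomised follow-up value of a score measured at entry, the entry value is the natural covariate. Leaving it out gives an unbiased comparison, but a less precise one if the entry value is prognostic. The SAP is still to be finalised, but the article has already named the primary test, so this is a comment on a stated choice and not on missing detail.

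What is at stake is the width of the interval for the main result and the power if the true difference is smaller than planned. The sample-size section allows for that possibility: it plans for 30 points where the reference study showed 35, and says that "patients in treatment arm 1 are likely to achieve up to 70 % remission".

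**Working it through.** **Inputs from the article.** Remission: "patients in treatment arm 1 are likely to achieve up to 70 % remission" and "treatment arm 2 approximately 40 % remission". Two-sided 5 % test, 80 % power, 10 % dropout, at least 49 per arm, raised to 60.

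**1. The plan's own figure.** With p1 = 0.70, p2 = 0.40 and mean 0.55:

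n = [1.960·√(2·0.55·0.45) + 0.842·√(0.70·0.30 + 0.40·0.60)]² / 0.30² = (1.379 + 0.565)² / 0.09 ≈ 42 per arm.

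With 10 % dropout, 42 / 0.9 = 46.7, so 47. The stated 49 is reproduced to within two patients.

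**2. Power of the unadjusted test at 70 % v 40 %.** Power = Φ[(0.30·√n − 1.379) / 0.671].

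- n = 44 (49 less 10 %): Φ(0.91) = 82 %
- n = 54 (60 less 10 %): Φ(1.23) = 89 %
- n = 60: Φ(1.41) = 92 %

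The stated 80 % is met without adjustment.

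**3. What adjustment could add.** The article gives no prognostic strength, so a range is assumed. The simulation model is logit P(remission) = a(arm) − b₁·z + b₂·s. Here z is standardised baseline DAS28, s is serostatus (75 % seropositive assumed), and a(arm) is set so that the marginal remission rates hold. From none to very strong, b₁ = 0, 0.3, 0.5, 0.8, 1.1 (odds ratio per SD exp(−b₁) = 1.00 to 0.33) and b₂ = 0, 0.2, 0.3, 0.5, 0.5. There were 60 per arm and 8,000 trials per cell. The chi-squared test was compared with the likelihood ratio test for arm in a logistic model containing both covariates. Entries are power in %, chi-squared → adjusted. The last column is the variance of the risk difference, unadjusted divided by adjusted (standardised), across the three settings.

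| Assumed strength (OR per SD) | 70 v 40 | 65 v 40 | 60 v 40 | Variance ratio |
|---|---|---|---|---|
| None (1.00) | 91.8 → 91.4 | 79.8 → 79.0 | 60.9 → 59.9 | 0.98 |
| Weak (0.74) | 92.6 → 92.9 | 80.3 → 80.1 | 60.7 → 60.7 | 1.00–1.01 |
| Moderate (0.61) | 92.6 → 93.6 | 80.0 → 81.5 | 61.9 → 63.5 | 1.03–1.05 |
| Strong (0.45) | 92.1 → 94.3 | 80.5 → 84.8 | 61.1 → 65.4 | 1.11–1.14 |
| Very strong (0.33) | 92.8 → 96.3 | 80.0 → 86.9 | 61.3 → 69.6 | 1.20–1.21 |

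Monte Carlo standard error: √(0.92·0.08/8000) = 0.3 points in the first power column, √(0.61·0.39/8000) = 0.5 in the third. A variance ratio of 1.20 is equivalent to 60 × 1.20 = 72 per arm.

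**4. Sensitivity of these figures.**

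- *Wald test.* Pooling by Rubin's rules leads to a Wald-type test, whose power was up to 1.2 points below the likelihood ratio test. At 60 v 40 % it gave 60.9 → 59.2 with no prognosis and 61.3 → 68.4 with very strong prognosis, that is about −2 to +7.
- *Evaluable number.* With 54 per arm (4,000 trials) at 70 v 40 %, the change was +1 to +6 points (87.1 → 88.2 to 88.9 → 94.8). The full analysis set keeps 60 per arm, but an imputed outcome carries less information than an observed one, so the trial may lie between the two.
- *Serostatus.* With the odds ratio per SD at 0.45, giving serostatus an odds ratio of 1.65 left the variance ratio essentially unchanged (1.12 v 1.11 at 54 per arm, 1.10 v 1.11 at 60).
- *Type I error.* With both arms at 40 %, chi-squared gave 4.1–5.6 % and the adjusted Wald test 4.2–5.8 % (4,000 trials per cell, standard error about 0.3 points). Both are acceptable.

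**The case against.** The strongest reply is that nothing here is wrong. The chi-squared test holds its level, matches the sample-size calculation and has about 89–92 % power at the planned difference. The article treats predictors of remission as a question to be investigated, and the entry floor of DAS28-ESR above 3.2 may narrow the range of the covariate and so weaken it. If it is not prognostic, adjustment costs a little power. All of this stands, and it sets the weight of the point.

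A reader might infer more from the same passages. The article does not support these readings:

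- **That power is certainly being thrown away.** This needs a prognostic strength that the article does not give.
- **That chance imbalance undermines the test.** One standard error of imbalance is √(2/60) = 0.18 SD, but the 5 % error rate already allows for it. The absence of a named stratification factor in a condensed article also does not show that there is none.
- **That no between-arm effect will be reported.** *Analyses* promises differences with 95 % intervals. The reference to the odds is loose wording, evidently for the odds ratio.
- **That the test clashes with multiple imputation.** Averaging chi-squared statistics over imputations would inflate the error rate (6.9 % in a simulation with 10 % missing), but the article nowhere proposes this. A valid pooling rule exists (5.0 %), and such mechanics are left to the SAP.

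The reply does not remove the main observation. A baseline value of the outcome measure is on hand for everyone, the primary method is stated without it, and using it needs only a change of wording.

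**Conclusion.** The point holds as an efficiency improvement to a stated method. The unadjusted test is valid and adequately powered, and the planned conclusion does not depend on changing it.

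With 60 per arm, adjustment changes power by about −1 to +4 points at 70 % v 40 % and about −1 to +8 points at a 20-point difference. It is worth 0 to about 20 % in effective sample size. The upper ends need baseline DAS28 to be very strongly prognostic (assumed odds ratio 0.33 per SD), and the larger power gain also needs a true difference well below 30 points. These figures rest on the assumed strengths, a normal covariate and the likelihood ratio test. The case rests on baseline DAS28-ESR; a separate gain from serostatus was not shown.

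**What to change.** Before database lock, and preferably in the SAP:

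- Make the primary analysis a logistic regression of week-48 remission on arm and baseline DAS28-ESR in the full analysis set, with serostatus optional. Keep the existing non-responder rule, fit the model in each imputed dataset and pool by Rubin's rules.
- Report the standardised risk difference, which is on the scale used for planning, and the odds ratio, each with a 95 % interval. State that the adjusted odds ratio is conditional on baseline DAS28. It is not the same quantity as the unadjusted one, which at the planned rates is (0.70/0.30)/(0.40/0.60) = 3.5.
- Keep the Pearson chi-squared test as a supporting analysis.
- In passing, change the wording from the odds to the odds ratio.

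The cost is one paragraph and no new data. A model-based test replaces a simpler one, and about 1 point of power is lost if the covariate is not prognostic (nearer 2 with the Wald version at a 20-point difference). The choice should be dated before lock, because made later it could look data-driven.
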